The atmosphere within the workplace of professionals has a direct influence on the quality of care, with immediate post-operative consequences in the case of failure [17]. This factor depends on the safety culture and the organization in the OR. Team work, communication, leadership and management by leaders are major determinants of the work climate. Local context and culture, characteristics of teams, along with local systems impact on frontline practice in the OR [18]. A change in existing norms and practices may be difficult to obtain [19]. Despite the specificity of this environment, OR staff practices may become routine, and staff may sometimes omit basic rules of discipline for patient safety.

Several guidelines refer to specific types of behaviour as potential risk factors for POC [20, 21]. National recommendations emphasize the importance of discipline during surgical procedures [22]. However, these recommendations are often vague, based on expert recommendations, without robust scientific evidence. The current literature suggests high variation in door-opening events during surgery (among which one third are considered avoidable) [23]. Opening doors may lead to airborne contamination and a subsequent increased risk of SSI [24, 25]. This risk is major during surgery involving a cutaneous approach, and belonging to the clean contamination class (Altemeier’s class I), such as orthopaedic or cardiac surgery. These data were recently confirmed by a multicentre observational study performed in France using new technological tools, describing correlation between entries/exits in the OR (median 29/h in orthopaedic surgery, minimum–maximum 16–65), staff movements and air particle counts [11]. The atmosphere in the OR seems to also be critical for patient safety. A noisy environment during procedures has consequences on patient comfort, anaesthesia and surgical practices [26, 27]. Hence, a high level of noise is associated with the occurrence of intra-operative and post-operative adverse events including SSI [28–30]. Initiatives to reduce the level of noise during procedures have led to improvement in patient safety [31]. However, to date, no interventional study using an adequately robust method (randomised controlled trial) has demonstrated the impact of improvements in intra-operative behaviour on the prevention of POC, including SSI.

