A multidisciplinary team will be created in each centre including orthopaedic surgeons, anaesthesiologists, surgical nurses and quality coordinators, who will be mentored by a lean coach (either infection control specialist or quality coordinator) during the entire intervention period. Each centre will designate a local project liaison and a local project champion. Project liaison will be an infection control/quality and safety specialist and the project champion a member of the OR staff (surgeon or nurse) with strong leadership skills. This adaptive method will be divided into 8 successive phases:Clarifying the problem: the baseline data collected before the intervention period by the monitoring system in the ORs will set the context in each centre/OR and across centres/ORs.Specifying the current situation: the reasons for door opening and assessment of communications, interruptions and distractions will be audited by members of the multidisciplinary team, including the local project liaison and champion, using validated observation forms [34, 35].Multidisciplinary analysis of data collected during the audits: these data will be presented and discussed to illustrate the baseline situation. The following questions will be addressed by the multidisciplinary team: who is opening doors/distracting/interrupting and for what reason; what is the variability among senior surgeons; when do the events occur.Determining the target condition: the multidisciplinary team will state the ideal conditions in term of door opening and noise levels (e.g. zero door opening between the time of the incision and closing of the wound, except for specific clinical reasons, namely a need for x-rays, unexpected materials, instruments or blood products; breaks or service shifts of employees; emergencies and/or supervision for the orthopaedist or anaesthetist).Analysing the root cause(s): the multidisciplinary team will analyse the gap between the baseline and the target conditions using an Ishikawa diagram, also known as a fish-bone diagram or cause-and-effect diagram [20]. This diagram uses the major categories “people, machines, methods and materials” to analyse the reasons for events.Action plan: taking countermeasures.Evaluating the impact of the action plan using the monitoring system.

Table 1 provides a further overview of the intervention as per TIDieR criteria.

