### Control conditions

As for the intervention arm, the monitoring system will be installed in the 15 orthopaedic centres participating in the control arm. Thus, data on door opening and noise levels will be collected for every hip/knee arthroplasty. However, these centres will be blinded to the data, the application and the dashboard. Intervention materials and training (e.g. slide shows, videos, posters), and the methodology of the adaptive approach will not be provided.

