### Outcomes

The primary outcome is the occurrence of any major POC (i.e. a composite of SSI, thromboembolic complications, unplanned surgical revision, in-hospital mortality, myocardial infarction, cardiac failure, stroke, renal failure/dialysis and sepsis) (Table 2) during the postoperative period, up to 30 days after the procedure (90 days for SSI). We will also evaluate readmission for any cause within 72 h after initial hospital discharge, ICU admission and in-hospital mortality during readmission. Secondary outcomes will include each of the individual components of the composite described above [37]. The registry-based design uses routinely collected data to ascertain our outcomes. In France, we have databases of routinely collected data on hospital discharge (acronym PMSI, hospital billing records) and *International Statistical Classification of Diseases and Related Health Problems, 10th Revision* (ICD-10) details. Algorithms previously built for the analysis of these databases will be used to assess the patient outcomes [6, 38]. A complementary analysis will be performed using specific algorithms for SSI [39]. Specialists in charge of this analysis will be blinded to the randomisation arm. Secondary outcomes are the occurrence of POC including whole individual items of the composite criterion, the occurrence of SSI or any wound complication (superficial, deep, organ/space, or a problem of healing) up to 90 days following the procedure, the number of door openings, and the level of noise automatically collected by a network of sensors placed in the OR.

**Table 2 Tab2:** Patient comorbidities and post-operative complications obtained from the French National Hospital Discharge Database and the *International Statistical Classification of Diseases and Related Health Problems, 10th Revision* (ICD-10)

Patient characteristics/comorbidities	Post-operative complication
Age	Surgical site infection
Gender	Thromboembolic complications
Public/private centre	Unplanned surgical revision
Elective/emergency	In-hospital mortality
Hypertension	Myocardial infarction
Ischemic heart disease	Cardiac failure
Cardiac arrhythmia	Stroke
Chronic heart failure	Renal failure/dialysis
Heart valve disease	Sepsis
Peripheral vascular disease	ICU admission
Dementia	Readmission within 72 h of discharge
Cerebrovascular disease	In-hospital mortality during readmission
Hemiplegia or paraplegia	
Chronic obstructive pulmonary disease	
Pulmonary circulation disorder	

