### Study timeline

The study will start with a baseline period of 3 months during which data on door opening and noise levels will be collected in the 30 ORs included (Fig. 2). The intervention period will last 6 months per centre. The centres will be included in two successive phases: a first phase including 15 centres (7 in the intervention arm and 8 in the control arm) and the 15 remaining centres in a second phase (8 in the intervention arm and 7 in the control arm). These two phases will be separated by a baseline period of 3 months (Fig. 2). This choice has been made for logistic reasons, to ease the installation of monitoring systems and the implementation of the intervention in a smaller group of centres. A post-intervention period of 6 months, keeping the monitoring system in place in the 30 ORs, will be used to assess the sustainability of the intervention. Due to the delay in the coding process of hospital discharge data and ICD-10 codes, we will analyse the outcomes at the end of our trial only.

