### Statistical methods

#### Data analysis

The results from the statistical analyses will be reported according to the Consolidated Standards of Reporting Trials (CONSORT) statement recommendations and its extensions for cluster randomised trials and for non-pharmacological interventions. No interim analysis will be performed. All eligible patients will be taken into account according to the initial allocation. OR, surgeon and patient characteristics will be reported using descriptive statistics. The primary outcome will be analysed using a logistic mixed model taking into account the stratification factor as a fixed effect [40]. Patients will be the unit of analysis and will be considered embedded with surgeons who will themselves be considered embedded in orthopaedic centres. Adjusted analyses may also be performed, notably in the case of baseline imbalance, a situation often encountered in cluster randomised trials, notably due to a limited number of randomisation units. A sensitivity analysis may also be planned depending on the results observed as regard to the adherence to the intervention. Intraclass correlation will be estimated within each group.

For secondary outcomes, components of the primary outcome will be analysed with an equivalent method as for the main criteria. The frequency of doors opening will be analysed with a mixed effect Poisson regression model with the duration of procedure as offset. The duration of hospital stay and the surgical intervention duration (from wound incision to closure) will be analysed using a mixed linear model after application of a Box-Cox transformation if necessary.

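### The stated door-opening model names no baseline term although both arms are monitored for three months beforehand; pre-specifying the baseline rate as a covariate is a nearly free gain in precision

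*Protocol article*

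**What the plan says.** Under Study timeline, the protocol article plans a "baseline period of 3 months during which data on door opening and noise levels will be collected in the 30 ORs included". Under Component 2, it says that "the baseline data collected before the intervention period by the monitoring system in the ORs will set the context in each centre/OR". Control centres are measured too: "the monitoring system will be installed in the 15 orthopaedic centres participating in the control arm" (Control conditions), although they do not see their data.

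The secondary outcomes include "the number of door openings, and the level of noise automatically collected by a network of sensors placed in the OR" (Outcomes). For door opening, Data analysis states: "The frequency of doors opening will be analysed with a mixed effect Poisson regression model with the duration of procedure as offset". No model is stated for noise. The only provision that touches baseline adjustment follows the primary-outcome model in the same section: "Adjusted analyses may also be performed, notably in the case of baseline imbalance". It names no covariate.

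On the spread to expect, the Background cites an earlier French multicentre study with a "median 29/h in orthopaedic surgery, minimum–maximum 16–65" openings per hour.

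**The concern.** Door traffic probably depends on features that persist from one quarter to the next, such as room layout, number of doors and local organisation. Study setting places no restriction on room size or door count, and randomisation is stratified by hospital type only. Differences between centres are therefore likely to supply most of the standard error of the arm comparison, and a centre's own earlier rate is the natural covariate for removing them.

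The article collects that covariate in all centres. For door opening, however, the only use it names is inside the intervention, as the starting point of the lean cycle. Control centres do not receive that method, so their baseline door data have no stated use.

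The stake is the second secondary objective: whether the bundle changed behaviour in the operating room. An imprecise answer there makes the trial harder to interpret if complication rates turn out not to differ.

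**Working it through.** **The plan's own figure.** The article gives no power or precision figure for door opening. Its only sample size is for the primary outcome, and it reproduces. For 10% against 7% with unpooled variance, 80% power and two-sided 5%, the result is 1353 per arm, or 2706. The design effect is 1 + (54.5 − 1) × 0.05 = 3.675, and 2706 × 3.675 = 9944.6, i.e. 9945. Nothing below changes this; it is used only for the number of procedures per centre.

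**Inputs from the article**
- Centres: "a first phase including 15 centres (7 in the intervention arm and 8 in the control arm"), then 8 and 7 in the second phase, so 15 per arm.
- Procedures per centre in six months: 9945 / 30 = 331.5. At the same pace, the three-month baseline gives about 166.
- Spread of rates: 16 to 65 per hour.

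**Assumptions, not in the article**
- The quoted range reflects differences between centres and spans about 4 SD on the log scale: ln(65/16) / 4 = 1.40 / 4 = 0.35.
- r, the correlation between a centre's baseline and intervention-period log rates, lies between 0.3 and 0.9.

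**Formulas**
- Unadjusted SE of the log rate ratio = SD × √(2/15) = 0.35 × 0.365 = 0.128.
- Adjusted SE = 0.128 × √(1 − r²), so the variance falls by r².
- Rate ratio detectable with 80% power = exp(−2.80 × SE), with 2.80 = 1.96 + 0.84.

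| r | Variance removed | SE | Detectable rate ratio | Detectable reduction | Equivalent multiple of centres, 1/(1 − r²) |
|---|---|---|---|---|---|
| no adjustment | – | 0.128 | 0.699 | 30% | 1.0 |
| 0.3 | 9% | 0.122 | 0.710 | 29% | 1.1 |
| 0.5 | 25% | 0.111 | 0.733 | 27% | 1.3 |
| 0.6 | 36% | 0.102 | 0.751 | 25% | 1.6 |
| 0.8 | 64% | 0.077 | 0.806 | 19% | 2.8 |
| 0.9 | 81% | 0.056 | 0.855 | 14% | 5.3 |

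With t multipliers on 28 degrees of freedom (sum 2.90 instead of 2.80), the unadjusted figure is about 31% and the r = 0.8 figure about 20%.

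**Sensitivity**
- *Assumed SD.* If the range spans 3 SD (SD 0.47), the detectable reduction goes from 38% to 25% at r = 0.8. If it spans 5 SD (SD 0.28), it goes from 25% to 16%. The percentage of variance removed does not depend on the SD.
- *Sampling error in centre means.* With a within-centre log SD of 0.5 between procedures, a true correlation of 0.8 is attenuated only to 0.793, and the variance ratio is 0.37 instead of 0.36.
- *Cost of estimating the slope.* This inflates the variance by roughly 1/24, about 4%, so adjustment breaks even at r of about 0.2.

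**The case against.** The strongest reply is that the sentence on door opening is condensed. It gives a model family and an offset. It does not spell out the arm term, the random effects, the stratification factor or the periods analysed, so a baseline term may stand in a full analysis plan that is not shown. That stands as far as it goes: the article does not establish that intervention-period counts alone will be compared. But this is the model the article states, it leaves out a covariate that the design goes to the trouble of collecting, and naming it costs nothing.

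A second reply points to the optional adjusted analysis. It does bear on chance imbalance, but it is discretionary, tied mainly to what is observed, and names no baseline rate. Adjustment chosen after seeing the data does not secure the precision in advance and leaves room for selective analysis.

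Third, the inputs to the absolute figures are weak. The Background does not say whether 16–65 per hour spans centres, rooms or procedures. If it spans procedures, the centre SD is overstated. Stratification by hospital type may already remove part of the spread. Both points stand, and the detectable reductions are illustrations only.

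Four stronger conclusions might be inferred, and the article supports none of them:
- *That most of the precision is lost.* Removing more than half the variance needs r above about 0.71. A high r is plausible, since the same centres are measured twice, but no value is given.
- *That the planned comparison is biased.* Under randomisation it is not.
- *That the noise analysis omits the baseline.* No noise model is stated that could omit it.
- *That a null result on complications could not be interpreted.* The article plans four separate assessments of adherence, and the process data are analysed in any case.

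**Conclusion.** The point holds as one of efficiency and pre-specification in a secondary outcome. Baseline door-opening rates are planned in both arms, the stated model names no baseline term, and the fallback is optional. Adjustment would remove between 9% (r = 0.3) and 81% (r = 0.9) of the between-centre variance of the log rate ratio. Where in that range the trial falls depends on r, which is an assumption. If the cited range does describe centres, the detectable reduction would move from about 30% to about 27% at r = 0.5, or 19–20% at r = 0.8. The calculation also assumes that baseline rates are recorded before any intervention activity, as Component 2 describes. The primary outcome and its sample size are unaffected.

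**What to change.** Pre-specify the centre's log baseline door-opening rate as a covariate in the mixed-effect Poisson model, alongside the arm term and the duration offset. Where a baseline exists for the individual operating room, its rate can be used instead. The article leaves that coverage unclear: Study timeline speaks of 30 operating rooms, Sample size of 65 in 30 facilities. The centre-level rate is therefore the safer default. When noise is analysed, use the baseline-period noise level in the same way.

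Fix this before outcome data are examined, and do not make it depend on observed imbalance. An analysis without the covariate can be reported beside it.

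The cost is one covariate per model in the analysis code and a sentence in the analysis plan. The data are already to be collected, and sites have nothing further to do. If r turned out to be very low, the loss would be about 4% of the variance.

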#### Data monitoring, harms and auditing

We do not have a data safety and monitoring board because our trial poses minimal risk. We do not plan to conduct any interim analyses for our primary outcome. Any unintended effect of the trial intervention will be tracked by weekly calls with the participating sites. The Nantes University Hospital, Sponsor of the study, provides insurance in case of negligent harm. We will not conduct any audits of trial conduct. Independent scientific experts will be part of the study scientific committee to provide external advice on the conduct and reporting of the study.

### Ethics

#### Consent, confidentiality and access to data

We will follow the Ottawa Statement on the ethical design and conduct of cluster randomised trials [41]. Our intervention will be delivered at the cluster level (operating theatre) and we were approved for an alteration of the individual patient and staff consent. The Tri-council Policy Statement on the Ethics for Research Involving Human Participants indicates that an alteration of individual informed consent is permitted when the research involves minimal to no risk to participants [42]. The alteration is unlikely to adversely affect the welfare of participants, and it is impracticable to carry out the research given the cluster-level intervention and research design if the prior consent of patients and staff (including surgeons) is required. We obtained a waiver of consent from our Research Ethics Board (Nantes University Hospital, Groupe Nantais d’Ethique dans le Domaine de la Santé) for data collection because we are not obtaining any identifiable private information from patients and staff. Participating patients will be informed by the surgeon or the anesthetist in charge before the surgical procedure, using an information letter validated by our Research Ethics Board. OR staff will be informed by an information note and enhanced communication.

Data on the surgical environment (OR characteristics and surgeons) will be collected on a paper form. A code will be attributed to surgeons in each centre. The link between the code and the surgeon identity will be kept by the investigators. These documents will be stored in a closed cabinet.

The network of sensors used for the monitoring of door opening and the noise levels collect aggregated data without the possibility of identifying individuals. These data will be stored on a dedicated secure server. Data on surgical procedures (patient ID number, type of procedure, date, incision time, wound closure time and the OR ID) extracted from OR information systems will be downloaded onto a dedicated server (Hestia) housed at the Nantes University Hospital, providing automatic encryption. Behavioural data and data on procedures will be merged on this server with the date and time of the procedure as a key variable (Fig. 3).

Hospital discharge and ICD-10 databases will be quarterly extracted from centres and stored on a dedicated server (Hestia) housed at the Nantes University Hospital, after automatic encryption of the patient ID number. The merging of these databases with the procedures and behavioral databases will be performed using the encrypted patient ID number as the key variable (Fig. 3). Finally, the encoded, linked, national administrative healthcare databases will be stored on the dedicated server housed at the Nantes University Hospital (see the “Data collection” section).

We received ethics approval from the “Nantes University Hospital, Groupe Nantais d’Ethique dans le Domaine de la Santé” to conduct the intervention. We obtained ethics approval from the “Comité National Informatique et Liberté” to obtain encoded baseline and outcome data on patients. “Comité National Informatique et Liberté” provides approval for research projects using the collection, storage, and use of hospital databases.

### Dissemination policy, authorship eligibility and data sharing plans

We aim to publish our findings regardless of negative or null results. All named authors in the protocol will be offered participation in the paper on final outcomes and any subsequent papers. We will not use any professional writing services. Due to institutional policies, we will not be able to grant public access to the participant-level dataset. We may be able to provide a statistical code. We will grant public access to all intervention materials.

### Trial status

This article refers to the protocol version 2 dated 6 November 2018. The recruitment will begin on 2 January 2019, with completion of recruitment expected in February 2020.

## Discussion

In the present protocol, we suggest the implementation of a cluster randomised trial to assess the impact of a bundle of measures based on the monitoring and feedback of intra-operative behaviour combined with an adaptive approach for their optimization, to prevent POC. We will adopt key points of behavioural change theories providing goal-setting, feedback and action planning in changing surgical staff behaviour in the OR during procedures [43]. The monitoring system, with connected wireless sensors developed and designed for the study, will provide staff with feedback on their behaviour and represent the corner stone of the intervention. Added measures will take inspiration from successful experience in the field [23]. The CUSP used in different areas for improvement in the quality of care, including surgery, will also represent a source of inspiration [44]. This strategy will help in the design of adaptive work, managing the staff’s attitudes and values, and engaging senior executives in patient safety initiatives [45].

Orthopaedic surgery involving knee and hip arthroplasty has been included according to the following criteria: a cutaneous approach, clean contamination class (Altemeier’s class I) and the frequency and the reproducibility of the procedure. An additional argument for this choice is the strong concern and awareness of orthopaedic surgeons about the risk of POC, especially infections. However, the methodological disadvantage of orthopaedic surgery is the low incidence of POCs. In consequence, the number of procedures to include is relatively high with an expected number of 9945 procedures in total. To ease the implementation of the protocol, data will be passively collected. All comorbidities and POCs will be identified using the local and national hospital discharge database, giving the possibility to follow patients 30 and 90 days after the procedure in all HCFs. Previous studies have demonstrated the feasibility and applicability of this method [6, 46]. One main limitation of this strategy is the potential misclassification of outcomes. Underestimation of their frequency remains possible; however, this would be expected to be similar in both groups. Nevertheless, we cannot completely exclude differential misclassification between the intervention and control groups.

We chose to select two behaviour surrogates for this study: the frequency of door opening and the level of noise. This selection was performed in a spirit of simplifying messages and data collection. Doors opening may be considered a surrogate of the organisation and discipline in the OR while the level of noise is a surrogate of the atmosphere and communication. Both are essential for effective conduct of the surgery. However, this has to be balanced so as not to fall into the excess of entries/exits and interruption/distraction, with potential consequences for the contamination of the environment and the performance of the surgical team.

Expected outputs from this study will be, first to build interventions based on an innovative tool to optimise staff awareness and behaviour according to the context and constraints of surgical activities. Second, this will also potentially demonstrate, using an accurate method, the impact of intra-operative behaviour on patient outcomes. Third, this will allow establishment of a standard of behavioural best practice in the OR. Finally, it will provide a broad evaluation of practices across a large panel of orthopaedic centres with an assessment of the benchmarking process. A reduction, even modest, in POC rates may have important consequences in term of public health, and will probably lead to the evolution of perception and measures for the control of intra-operative risk. The field of discipline in the OR appears poorly explored and seems to represent an interesting and promising way to improve surgical performance in the future.

This challenging project gathers specialists from several disciplines (infection control, epidemiology, surgery, anaesthesiology, psychology and engineering) and will confirm or disprove the impact of intra-operative staff behaviour on the occurrence of POC. Even if applied in orthopaedic surgery and knee/hip replacement, the findings may be transposable to other surgical specialties and procedures with potentially broad application of the monitoring/feedback system and adaptive approach for the optimisation of intra-operative behaviour.

